### Follow-up (8 weeks ± 3 days after visit 4)

A follow-up phone call to assess or follow up on any adverse events reported during the study.

### Qualitative assessment

A series of semi-structured interviews with staff having used the device will be undertaken to obtain feedback from the different stakeholders on the experience of working with the device, benefits seen/expected, any unintended consequences of use, suggestions for improvement and willingness to keep using it. All interviews are to be recorded, transcribed and then coded—independently by two researchers and then together where codes will be refined, combined and categorized to create themes and trends.

Sample size in each group is determined by saturation of themes—usually involving 5–12 interviews with different stakeholders.

Stakeholders are:Nursing home manager/director, care manager, quality manager (management NH).Nurse (registered nurse, licensed professional nurse).Care aide (healthcare aide, personal support worker).

From the perspectives of these stakeholders, the benefit of the device is to be considered for the resident but also for the stakeholder.

### Sample size {14}

Due to the complexity of the study design with respect to power estimation, a sample size calculation was performed via simulation using SAS 9.4. Resident-level baseline and treatment profiles were generated according to best estimates of care event counts and skin health behaviours. Cluster-wide effects were added to the simulated responses such that an intra-cluster correlation (ICC) of 25% in both co-primary endpoints was present. Plausible values for the ICC were considered based on published results in Lee *et al.* [23].

A simulation set of 1000 hypothetical studies, with cluster sizes varying at random between 3 and 9 residents uniformly, was generated. Assuming an average decrease (i.e. improved efficiency) in the care efficiency score of 20% (σσ = 7.3%) as compared to usual care and an average reduction (i.e. improved skin health) of 0.2 (σσ = 0.3) in skin health grade as compared to usual care, a sample size of 16 clusters in total yields a power of 86.4%. To allow for cluster loss and to maintain a balanced study design, 20 clusters will be recruited, 10 in Canada and 10 in Germany. Based on the average site capacity, these 20 clusters correspond to approximately 180 individual residents. Caregivers will be recruited from the participating care units; we anticipate having at least 8 caregivers per cluster being able to contribute to the study or 160 caregivers in total.

### Recruitment {15}

NH will be recruited using a list of homes within 100 km of the trial centre in each country. The trial centre will prepare letters and information packages including guidance on the eligibility criteria and requirements for study participation. The director of care/site administrator or equivalent is the primary recipient of the initial information. One week after the first contact, the trial centre will follow up the contact and explain the study and address any questions. If the site is interested in participating, a visit will be arranged. Study team members will visit the site to provide further information about the study and answer questions. An agreement will be initiated and the site, subject to any required internal approval mechanism, will give written consent to be part of the study. Should further clarification or internal consultation be required, a follow-up telephone call not later than 1 week following the visit can be conducted. Following consent of the site and a written agreement, the site can be enrolled into the study by trial research staff. Care units will be randomly allocated from amongst the general clinical units in each home. Residents will be recruited following the identification of potential participants by unit staff. Caregivers will be recruited by the researchers from the participating care units.

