**Fig. 1 Fig1:**
[figure not shown]
Components of the SmartCare Change Indicator: The electronic sensor (**B**) is placed on the outside of the incontinence product and estimates the urine saturation level. Results are displayed via an app and dashboard (**A**) installed on a mobile derive or desktop computer. **C** Detailed view on the transmitter which is combined with the sensor strip and placed on the incontinence product

Prior to any resident procedures, data on the degree of person-centred continence care, the current check and change routine, and estimates for the cost of treatment of skin injuries and for prevention of skin health will be collected. On each intervention unit, a team from the sponsor will then conduct standardized training on the use of the interventional device . Researchers will familiarize care staff on trial**-**related procedures and data collection requirements.

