### Visit 2: end of baseline (4 weeks ± 3 days after start of baseline)

At this visit, a data quality check will be made and remedial action taken should this be needed. An assessment of the resident skin health status will be made, and confirmation of skin health eligibility will be made.

Written informed consent from care staff will be obtained and data on care staff work engagement, organizational headroom [3 questions on staff availability assessed on a 5-point Likert scale], tasks rushed and left undone on that shift and reported resident quality of life will be collected (see measures below). Investigational devices will be provided and installed.

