### Concealment mechanism {16b}

To mitigate contamination between intervention and usual care groups and in line with the trial design, each NH will only be allocated to a single intervention.

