### Assignment of interventions: who will be blinded? {17a}

There will be no blinding at the level of the resident, clinical care unit or NH. The trial statistician will be blinded to unit allocation.

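### As described, unblinded units are allocated before their own staff nominate residents and keep the baseline diary, and the concealment section states no safeguard

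*Protocol article*

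**What the plan says.** All references are to the protocol article.

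- **Order of steps.** Recruitment {15} goes from the home's consent and enrolment to "Care units will be randomly allocated from amongst the general clinical units in each home", and then to "Residents will be recruited following the identification of potential participants by unit staff".
- **Set-up and training.** The text after Fig. 1 in Intervention description {11a} opens the set-up stage with "Prior to any resident procedures, data on the degree of person-centred continence care" and continues: "On each intervention unit, a team from the sponsor will then conduct standardized training on the use of the interventional device".
- **Blinding.** Section {17a} states: "There will be no blinding at the level of the resident, clinical care unit or NH". Only the trial statistician is blinded.
- **Concealment.** Section {16b} gives contamination as its purpose and says that "each NH will only be allocated to a single intervention". Sections {16a} and {16c} add that randomization is central, with {16c} naming the sponsor, and do not date it relative to resident consent.
- **Staff input.** The responsive-behaviours exclusion draws on care-staff opinion. Caregivers receive the resident diaries at Visit 1. Table 1 takes the baseline of both co-primary endpoints from the final week of the baseline period, and the care events and daily skin grades behind them are diary entries.
- **Visit 2.** At the end of the 4-week baseline, skin is assessed and "confirmation of skin health eligibility will be made". Devices are installed at this visit, and Table 2 marks device handover and the instruction of site staff there and at no earlier visit.

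**The concern.** In a cluster trial, central randomization protects the sequence for homes and units. It does not protect the later choice of residents within them. If the people who nominate residents know their unit's arm, the two arms can differ in case mix before any device is used. That matters here because the care efficiency score depends on the resident's care-need group: the Table 3 task weights differ widely between groups.

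A cluster random intercept does not remove such a difference. An intention-to-treat analysis would not remove it either, because the difference arises at enrolment (the plan is per protocol in any case). Adjustment for baseline helps, but less so if the baseline diary is itself kept by staff who know their arm. Both co-primary comparisons rest on this diary.

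**Working it through.** **1. The passages side by side**

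| Question | What the article gives |
|---|---|
| Is allocation before resident recruitment? | Yes in the order of {15}. No date relative to consent in {15}, {16a} or {16c}. |
| Do units know their arm? | {17a} states no blinding of unit or home. |
| Who starts resident selection? | Unit staff ({15}); care-staff opinion also enters one exclusion. |
| Who records baseline? | Unit caregivers, in the diary handed out at Visit 1. |
| Is there a concealment step? | None in {16b}, which covers contamination. No other section has residents identified, consented or baselined before allocation is released, or assigns recruitment to someone blinded. |
| When are intervention units trained? | {11a}: directly after data taken before resident procedures. Table 2 and Visit 2: handover, instruction and installation at the end of baseline. The two do not agree. |

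The gap in concealment does not depend on how the last row is resolved. With training at Visit 2, nomination and baseline recording would still take place in units whose arm is, as described, already assigned and not blinded.

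**2. Illustration of sensitivity**

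The plan has no figure for this point, so there is none to reproduce. The stated 86.4% power is not in question here.

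Inputs from Sample size {14} and Statistical methods {20a}: ICC 0.25; 20 clusters, so 10 per arm; cluster sizes uniform from 3 to 9 in the simulation; about 180 residents expected; one-sided alpha 2.5%. Assumed, because the document gives no value: a selection shift of b standard deviations favouring the device, left uncorrected in the analysis.

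- Mean cluster size m = 6; variance (7² − 1)/12 = 4; cv² = 4/36 = 0.111.
- Design effect = 1 + (m(1 + cv²) − 1) × ICC = 1 + (6 × 1.111 − 1) × 0.25 = 2.417.
- Effective n per arm = 10 × 6 / 2.417 = 24.8.
- Standard error of the difference in SD units = √(2/24.8) = 0.284.
- One-sided type I error = Φ(b/0.284 − 1.96).

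At the expected 180/20 = 9 residents per cluster (equal sizes), the design effect is 1 + 8 × 0.25 = 3, effective n is 90/3 = 30, and the standard error is √(2/30) = 0.258.

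| Assumed shift b (SD) | Mean size 6 | Size 9 |
|---|---|---|
| 0 | 2.5% | 2.5% |
| 0.1 | 5.4% | 5.8% |
| 0.2 | 10.5% | 11.8% |
| 0.3 | 18.3% | 21.2% |

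These are normal approximations for the single superiority test of care efficiency.

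**The case against.** The strongest reply is that the sequence is inferred. The sentence on allocating units in {15} could partly mean choosing which unit takes part. Randomization is never dated relative to consent, and an article may leave the release of allocation to the full protocol. This stands as a limit on certainty. It does not supply a safeguard: the article has a section for concealment, and what it puts there is contamination control.

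Three stronger readings are tempting and are not supported:

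- **That the baseline diary is kept by staff already trained on the device.** This follows from the word order in {11a}, but Table 2 and the Visit 2 text point to the end of baseline. The passages must be reconciled; neither can be taken as settled.
- **That unit staff control eligibility generally.** Researchers take consent, the trial centre team conducts Visits 1 and 2, and Table 2 gives the visit skin assessments to an investigator. The general unsuitability exclusion is likewise tied to the investigator's judgement. The article does not say that these people are blinded, but the staff-driven route is narrower: nomination, opinion on one exclusion, and the diary.
- **That the Table 3 weights show selection could produce a given fraction of the 20% target effect.** The document gives neither event counts nor the mix of care-need groups, so any such percentage is invented.

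It is also fair to say that selection could run against the device, and that Table 1 defines a baseline for both co-primary endpoints. Adjusting for that baseline would absorb part of a case-mix shift, because the care-need weights enter the baseline score too.

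**Conclusion.** The point holds in limited form. As described, units are allocated before residents are recruited, they are not blinded, and their staff nominate residents and record the baseline of both co-primary endpoints. No safeguard is stated, and {16b} does not address concealment. Separately, {11a} conflicts with Table 2 and the Visit 2 text on when training takes place.

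The document does not show that bias will occur, in which direction, or how large it would be. The illustration (about 5% to 18% one-sided error for 0.1 to 0.3 SD with mean cluster size 6, somewhat more with 9) rests on an assumed shift, in the device's favour, with no correction. It shows that modest selection would matter at this sample size, and nothing more. The point is worth acting on because no later analysis can fully remove bias introduced at enrolment.

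**What to change.** In each home, complete resident identification, consent, eligibility and the 4-week baseline diary, including the Visit 2 eligibility check, before the centrally generated allocation is released to that home. Then train the intervention units and hand over devices. Because installation is already placed at Visit 2, no stated step requires the arm to be known sooner.

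Rewrite {16b} to describe this, and bring {15}, the training text in {11a}, Table 2 and the Visit 2 text into one consistent order. If this is already the practice, only the rewriting is needed.

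The cost is mainly logistic: existing steps are re-ordered and training is compressed around Visit 2. There is also a risk that a home withdraws on learning its arm after baseline, which matters with 20 clusters.

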### Assignment of interventions: allocation and sequence generation {16a}

Care units (clusters) at study sites will be randomly assigned 1:1 to the intervention and control arms. There will be one control or one intervention cluster at each study site. Randomization of NH and care units will be perfumed centrally using a computer-generated pseudorandom number table.

### Concealment mechanism {16b}

To mitigate contamination between intervention and usual care groups and in line with the trial design, each NH will only be allocated to a single intervention.

### Implementation {16c}

Randomization of NH and care units will be performed centrally by the sponsor using a computer-generated pseudorandom number table.

### Assignment of interventions: who will be blinded? {17a}

There will be no blinding at the level of the resident, clinical care unit or NH. The trial statistician will be blinded to unit allocation.

### Procedure for unblinding if needed {17b}

There is no blinding of the residents, clinical care unit or NH. The trial statistician will be unblinded after data analysis.

### Data collection and management

#### Plans for assessment and collection of outcomes {18a}

In addition to daily assessments of skin health and continence product usage, etc., data will be collected by researchers as outlined in the trial schedule (Tables 2, 3 and 4).

**Table 3 Tab3:** Time estimate (in minutes) for each continence care task dependent on the resident persona (see Table 4). The table is divided into day and night (21:00–07:00 local time). Values are used as the weight when calculating the care efficiency score primary endpoint

Day	Group 1	Group 2	Group 3	Group 4	Group 5	Group 6
Pad check	0	0	1	6	6	6
Pad change	0	0	7	8	10	20
Change of clothes	0	5	8	10	18	40
Change of bedlinen	0	2	2	8	18	20
Toilet visit	0	0	10	18	20	50
Night	Group 1	Group 2	Group 3	Group 4	Group 5	Group 6
Pad check	0	0	1	4	4	4
Pad change	0	0	7	8	10	20
Change of clothes	0	5	8	10	18	40
Change of bedlinen	0	4	4	10	10	20
Toilet visit	0	0	10	20	0	0

**Table 4 Tab4:**
[figure not shown]
Personae and resident grouping depending on care need

Grouping of persons with functional urinary incontinence. Orange shading indicates the driver of care needs. In addition to functional incontinence caused by the inability to self-toilet due to cognitive and mobility issues, factors related to the bladder or bowel function may increase the need for toileting and containment care and influence a decision as to the need for containment products

**Includes standing, walking and transfers to and from the toilet, as well as the ability to carry out personal hygiene

#### Plans to promote participant retention and complete follow-up {18b}

All residents and caregivers will be given the opportunity to ask questions about the investigation and will be given sufficient time to decide whether to participate in the investigation or not. During the trial, no additional actions to promote resident retention will be taken other than caregiver staff support and researcher visits according to protocol. If any new important information arises during the clinical investigation, the resident will be informed both orally and in writing.

### Data management {19}

Resident data will be recorded directly into a custom-designed electronic case record file (eCRF). Data from paper records and diaries will be entered into the eCRF. Questionnaires will be considered source data. There will be no data entry into clinical records within the nursing home. Programming quality control processes will include checks for potential issues during import of raw data into the analysis software. A data validation plan (DVP) specifies the check that is to be performed on resident data for the clinical investigation. When all data from all endpoints of all residents have been entered, discrepancies solved and all reconciliation with the safety database is complete, the database will be locked, and the data will be analysed. Imputation methods will not be applied to the study data. No formal testing of outliers will be performed. All residents from all clusters will be pooled for analysis Data management and handling will be conducted according to the investigation-specific Data Management Plan (DMP) in accordance with applicable guidelines and standard operating procedures (SOPs). Any deviations, i.e. discrepancies and additions from the process defined in the DMP, will be described in an investigation-specific data management report (DMR).

### Confidentiality {27}

All data handling is in accordance with the European Union General Data Protection Regulation (GDPR) 2016/679 and the Canadian Personal Information Protection and Electronic Documents Act (PIPEDA). By fulfilling PIPEDA, the device also covers the Alberta Freedom of Information and Protection of Privacy Act and Health Information Act. All study data submitted to the sponsor will be de-identified. An identification list of participants will be kept separately and securely in password-protected, encrypted computer files.

### Statistical methods for primary and secondary outcomes {20a}

The primary analysis will be at the cluster level while some secondary endpoints are at the resident or caregiver level. The significance level for one-sided testing and confidence intervals is set to 2.5% while two-sided testing and confidence intervals are set to 5%.

Demonstration of the treatment effects on both primary endpoints is considered necessary for the demonstration of clinical benefit (co-primary endpoints).

The care efficiency and skin health co-primary endpoints are evaluated using linear mixed models (LMMs) to account for intra-cluster correlation using a random intercept effect. For each primary endpoint, the treatment effect is quantified using the difference in the least squares means of the treatment groups. For the care efficiency score, superiority is assessed by a one-sided test of the group mean difference where no superiority margin is added. For the skin health score, non-inferiority is assessed by a one-sided test of the group mean difference where a non-inferiority margin of + 0.5 will be used. Analysis will be per protocol. There are no plans for an intention-to-treat analysis.

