## Methods: participants, interventions and outcomes

### Design {8}

The study is a multinational multi-site, prospective parallel open-label cluster randomized trial with comparator groups comprising control (usual care) and intervention (device). Clusters, at the level of the nursing home clinical care unit, will be allocated to either intervention or usual care in a 1:1 ratio.

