### Criteria for discontinuing or modifying allocated interventions {11b}

Residents are free to discontinue participation in the clinical investigation at any time and are.

not required to give a reason for their decision. However, residents who discontinue the investigation will be asked about the reason(s) for their discontinuation and about the presence of any adverse event (AE)/adverse device effect (ADE) and, if possible, be assessed by an investigator.

Specific reasons for the withdrawal of *residents* are:the decision of a resident, or alternative decision-maker on behalf of the resident to withdraw from the investigationthe investigator deems the resident unfit for the investigation

*Caregivers* (care aides, nurses) are free to discontinue participation in the clinical investigation at any time and are not required to give a reason for their decision. However, caregivers who discontinue the investigation will be asked about the reason(s) for their discontinuation.

Caregivers may be withdrawn from the clinical investigation and assessments at any time, if deemed necessary by the investigator.

*Care units* may be withdrawn from the study at the discretion of the investigator should he/she decide that the study procedures and protocols are not being adhered to and any action taken to remediate the situation results in no improvement.

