### Method in analysis to handle protocol non-adherence and any statistical methods to handle missing data {20c}

All residents from all clusters are pooled for analysis which will be performed using the last observation carried forward where subjects are lost before the final observation. Data from subjects requesting data removal on their early termination will not be included in the analysis. Imputation methods will not be applied to the study data. No formal testing of outliers will be performed.

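### Per protocol is the only planned analysis for both co-primary endpoints, including a superiority test, in an open-label cluster trial whose units can be withdrawn for non-adherence

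*Protocol article*

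**What the plan says.** All references are to the protocol article.

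- **Analysis set, {20a}:** "Analysis will be per protocol. There are no plans for an intention-to-treat analysis". The statement makes no distinction between the two co-primary endpoints.
- **Tests, {20a}:** for care efficiency, "superiority is assessed by a one-sided test of the group mean difference where no superiority margin is added". For skin health, "a non-inferiority margin of + 0.5 will be used". Both are one-sided at 2.5%, and both must succeed: "Demonstration of the treatment effects on both primary endpoints is considered necessary for the demonstration of clinical benefit".
- **Design, {8} and {17a}:** a "prospective parallel open-label cluster randomized trial". Residents, units and homes are not blinded. The trial statistician is the only role described as blinded.
- **Withdrawal, {11b}:** the rule for a whole care unit reads: "withdrawn from the study at the discretion of the investigator should he/she decide that the study procedures and protocols are not being adhered to". The sentence adds a condition, that attempts to put matters right have brought no improvement. Residents may also be withdrawn if the investigator judges them unfit.
- **Pooling and missing data, {20c}:** "All residents from all clusters are pooled for analysis", with last observation carried forward for those lost early. The same paragraph says that no imputation will be applied. Section {19} repeats the pooling and no-imputation statements.

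**The concern.** A superiority claim rests on comparing the groups that randomisation created. Here the article does more than leave the analysis set to a later document: it rules out the as-randomised analysis. Defining the per-protocol set carefully in an analysis plan would not restore it.

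The withdrawal rule gives the issue practical weight. The open-label design lets the investigator know the allocation. In Table 2 the investigator or trial centre team conducts the visits at which the device is handed over and its correct use confirmed. Not using the device is a form of non-adherence that usual care cannot show. Units where the device adds work are plausible non-users, and workload is what the efficiency score measures. The endpoint uses only the final intervention week, so a unit withdrawn before then contributes no final-week score.

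At stake is the error rate of the superiority test, and also what it estimates: the effect in units that complied, not the effect of introducing the device. Requiring success on both endpoints does not repair this. If skin-health non-inferiority truly holds and is tested with high power, the chance of a false overall claim is close to that of the efficiency test alone.

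**Working it through.** The plan gives no figure on this point to reproduce. Its 86.4% power for 16 clusters is a separate matter and is not challenged here. The check asks how far selective removal of units could move the one-sided error.

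**Inputs from the article.** There are 20 clusters allocated 1:1, so 10 per arm. Cluster sizes are uniform on 3 to 9 (mean 6), the ICC is 0.25 and the one-sided level is 2.5%. The plan powers on 16 clusters and recruits 20, leaving 20 − 16 = 4 spare, or two per arm. Losing one or two units in an arm is thus within the plan's own allowance.

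**Assumptions not in the article.** There is no true effect. One or two units are removed, all from the intervention arm. Removal is ranked on a variable that has correlation ρ with the unit's mean score. A t-test on cluster means stands in for the mixed model.

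**Spread of a cluster mean** (resident SD = 1):
- The average of 1/m over sizes 3 to 9 is 0.190.
- Variance = ICC + (1 − ICC) × 0.190 = 0.25 + 0.75 × 0.190 = 0.392.

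**Simulated result** (20,000 runs per cell; nominal 2.5%; 2.5% also obtained with no removal):

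| ρ | 1 of 10 removed | 2 of 10 removed |
|---|---|---|
| 0 | 2.5% | 2.5% |
| 0.3 | 3.5% | 3.7% |
| 0.5 | 4.0% | 5.3% |
| 0.7 | 4.6% | 7.1% |
| 1 | 6.1% | 11.2% |

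A repeat of the ρ = 0.5 row with 100,000 runs gave 3.8% and 5.2%.

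**Hand check at ρ = 0.5:**
- One unit removed: the simulated mean shift is −0.054. SE = √(0.392 × (1/9 + 1/10)) = 0.288. Shift/SE = 0.19, so the error is about P(Z < −1.96 + 0.19) = 3.8%.
- Two units removed: the shift is −0.097. SE = √(0.392 × (1/8 + 1/10)) = 0.297. Shift/SE = 0.33, so the error is about P(Z < −1.63) = 5.1%.

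Both agree with the simulation.

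**Balanced loss.** If one unit is lost from each arm at ρ = 0.5, the error is 2.7% and the mean difference is unbiased. The inflation therefore needs removal that is both uneven between arms and related to outcome.

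**Text side by side.** {20a} restricts the analysis to a per-protocol set. {19} and {20c} pool all residents of all clusters. The pooling sentence may only mean that sites and countries are combined. It does not promise analysis as allocated, so it does not override {20a}, but the analysed population is left unclear. Separately, {20c} calls for last observation carried forward and for no imputation. Carrying an observation forward is imputation, so those two statements conflict.

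**The case against.** Several stronger readings are tempting, and the article does not support them.

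- **Exclusions fall in the intervention arm only.** The trigger in {11b} is failure to follow study procedures, not failure to use the device. Both arms keep daily diaries and are barred from starting new incontinence medication, so control units can be withdrawn as well. The rule also applies only after remediation has failed. What stands is that the intervention arm has one additional way to fail.
- **The bias certainly favours the device.** The score is a weighted sum of recorded events per recorded diary day, and lower is better. A unit that under-records looks efficient, and removing it from the intervention arm would work against the device. The favourable direction is plausible, not shown.
- **An error of 6% or 11% is to be expected.** Those figures assume perfect selection on the endpoint itself. Withdrawal is decided on adherence, and a unit withdrawn early has no final-week score to be selected on.
- **{20c} flatly contradicts {20a}.** Given the reading of pooling as combining sites, the wording is ambiguous rather than contradictory.
- **Residents whose skin worsens will leave the per-protocol set.** {11b} names no such trigger.

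It is also fair to say that per protocol is a conventional set for non-inferiority, so the criticism bears mainly on the superiority endpoint. None of this answers the central point: {20a} leaves that endpoint with no as-randomised analysis at all.

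**Conclusion.** The point holds in a limited form. The plan analyses a superiority co-primary endpoint per protocol only, excludes intention-to-treat by an explicit statement, and allows discretionary withdrawal of whole units in a trial where allocation can be known. The protection of randomisation is given up for one of the two endpoints on which the benefit claim depends.

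The numerical consequence is conditional. It is nil if exclusions are unrelated to outcome. The one-sided error rises to about 4% or 5% with one or two intervention units removed at a correlation of 0.5, and to at most about 6% or 11% under perfect selection. How many units are lost, from which arm, and how strongly loss relates to workload are assumptions. That the investigator knows the allocation is inferred from the open-label design and not stated.

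**What to change.** 1. In {20a}, make the primary superiority analysis of care efficiency as-randomised: all enrolled residents of all randomised units with available data, analysed in the arm to which their unit was allocated.
2. For skin-health non-inferiority, report the as-randomised and the per-protocol sets and require consistent conclusions.
3. Fix the per-protocol exclusions before the data are analysed, while the statistician is still blinded, and report them by arm with reasons.
4. Continue collecting diaries from units that stop using the device, where this is feasible and consent allows. A unit withdrawn because it keeps no diaries cannot supply them, and {20c} excludes data whose removal a subject requests, so the rule for missing final-week data must be stated.
5. Reconcile {19}, {20a} and {20c} on who is analysed, and choose between last observation carried forward and no imputation.

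The cost is revised wording, one more analysis set and some continued data collection. The estimated effect may also be smaller. For example, if 2 of 10 intervention units did not use the device and gained nothing (an assumption), the planned 20% reduction would average 0.8 × 20% = 16% as randomised.
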